### Participants

The multidisciplinary team of specialists conducting the study will invite all consecutive MS patients attending their regular clinical follow-up visits at the Hospital Universitario de la Princesa in Madrid (Spain) to participate in the study. The participants will be screened for eligibility by the study supervisor according to the inclusion and exclusion criteria. Recruitment started in January 2020.

### Eligibility Criteria

Participants are eligible for the study if they meet the following inclusion criteria:

Aged 18 years or older.Diagnosis of MS according to revised McDonald criteria (35).Written informed consent to participate in the study.An Expanded Disability Status Scale (EDSS) (36) score between 2.5 and 7 and a score of ≥2 points in two of the following functional systems (FS): pyramidal, brainstem or cerebellum.≥1 point in the cognitive FS of the EDSS.Ability to engage and manage new technologies and use the headset.Own a compatible smartphone to install the VR program.Patients requiring medication which, in the investigator's opinion, may interfere with rehabilitation results, must be on a stable regimen at study entry. Note: Patients in whom this medication is modified during the study will be excluded from the study.

Patients who could benefit from a rehabilitation program.

Subjects who meet any of the following criteria will be excluded from study entry:

Participation in any clinical trial at the time of data collection.Cognitive impairments which, in the investigator's opinion, might pose difficulties for understanding and completing the study questionnaires or operating the VR system.Have had a relapse and/or have received methylprednisolone or equivalent within the last 30 days or during the study. Note: Patients who have a relapse or who are treated with this medication during the study, as described above, will be discontinued from the study.Have initiated pharmacological treatments that could modify the patient's walking ability within the last 30 days or during the study. Note: Patients who are treated with medication during the study, as described above, will be discontinued from the study.Any visual or hearing disorder that prevents correct use of the VR system.Diagnosis of any health condition which, in the investigator's opinion, prevents the completion or continuation of the rehabilitation program.

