## Methods

### Study Design

To test the study objectives, a prospective single-center 6-months follow-up study will be conducted in patients with MS. During this period, MS patients will be treated and/or evaluated by a multidisciplinary team of specialists including neurologists, physiotherapists, physiatrists, neuropsychologists and nurses. After patients have signed the informed consent form and have been confirmed to meet the selection criteria, they will be randomized 2:1 to the VRR group or the CR group. This unequal ratio has been used so that each subject entering the study has twice the probability of being assigned to the VRR group, which is expected to positively impact the patient experience with the rehabilitation program. In the VRR group, patients will receive 4 CR sessions plus 4 VRR sessions at the hospital during ~4 weeks. In the CR group, patients will receive 8 sessions of CR at the hospital during ~4 weeks. After the on-site rehabilitation, both groups will continue with rehabilitation at home for an additional 5 months. The VRR group will receive a VR headset and the CR group will receive instructions on CR techniques and a notebook with cognitive tasks. Figure 1 shows an overview of the study design.

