**Figure 1 F1:**
[figure not shown]
Study design.

The randomization lists will be created using the EPIDAT statistical software developed by the *Servicio de Información sobre Saúde Pública de la Conseller*í*a de Sanidade e Servicios Sociais de la Xunta de Galicia* (Spain) and the *Special Program for Health Analysis* (SHA) of the Pan American Health Organization (PAHO). A permuted block design with a computer random number generator will be used. The neurologist, physiatrist, and neuropsychologist involved in the assessment of the patient will be blinded to randomization. The physiatrist, physiotherapist, nurse, and neurologist treating the patient will be aware of the randomization. Both randomization and blinding are not required to achieve the primary aim of the study. However, we decided to randomize the patients to prevent selection bias and allow comparisons between groups (secondary aims). Blinding was also considered to be appropriate in order to increase the objectivity of the neurologist and neuropsychologists involved in patient assessment.

The number of study visits will be up to 4. A screening visit (V_0_) where the patient will be invited to participate in the study after being informed of its characteristics, a baseline visit (V_1_) where training on the VRR or CR will be conducted, a post-rehabilitation on-site visit (V_2_), and a post-rehabilitation at-home visit or study competition visit (V_3_). All visits will be conducted at the time of routine clinical practice visits. The screening visit (V_0_) and baseline visit (V_1_) might be combined, and in that case the total number of study visits will be 3.

The study was approved by the Ethics Committee of the Hospital Universitario de la Princesa on 26/09/2019 and will be conducted in accordance with the ethical standards laid down in the 1964 Declaration of Helsinki.

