#### Clinician-Reported Outcomes

A variety of clinician-reported outcomes (ClinROs) will be collected at the baseline visit (V_1_), post-rehabilitation on-site visit (V_2_), and a post-rehabilitation at-home visit or study competition visit (V_3_) by a neurologist unaware of the rehabilitation group allocation. Changes from the baseline visit (V_1_) to month 6 (V_3_) and from the baseline visit (V_1_) to month 1 (V_2_) will be collected as secondary and exploratory variables, respectively. ClinROs were selected on the basis of previous studies of rehabilitation that reported statistically significant improvements by using VRR in disability (17, 18), spasms and spasticity (40), and balance (19, 24, 33).

Disability progression will be evaluated by the EDSS (36), the Nine-Hole Peg Test (9-HPT) (41), the Timed 25-Foot Walk (T25-FW) (42), and the Six-Minute Walk Test (6 MWT) (43). The EDSS (36) assesses 7 functional systems based on a neurological examination. The score ranges from 0 to 10 in 0.5-unit increments that represent higher levels of disability. The 9-HPT (41) tests upper extremity function. Patients will be instructed to place pegs from a container one by one into each of the nine holes of the board as quickly as possible. The score is the average time required in four trials (two trials for each hand). It is one of the three components of the MS Functional Composite (MSFC) disability assessment (42). No specific cut-off score has been validated for MS (44), but a worsening of 20% on all the measures of the MSFC is generally accepted to indicate disease progression. The T25-FW (42) evaluates mobility and leg function performance based on the time until the patient reaches the 25-foot mark (7.62 m). Patients will start at a line on the floor and will be instructed to walk as quickly as possible but safely beyond the second line 25 feet away. The score is the averaged time of 2 trials, and the time limit per trial is 3 min. It is another of the three components of the MSFC disability assessment (42). The 6 MWT (43) measures the distance walked over a span of 6 min. Patients will be instructed to walk at a comfortable pace back and forth along a 60-foot walkway for 6 min (43).

Spasms and spasticity will be assessed by the Modified Ashworth Scale (MAS) (45). This scale measures resistance during passive soft-tissue stretching. It consists of a 5-point nominal scale using subjective clinical assessments of tone ranging from 0 to 4.

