### Sample Size Calculations

Sample size calculations were conducted using the Granmo v7.11 software. No previous studies using the USEQ in patients with MS have been performed, so assumptions had to be made for estimation of the sample size. Since the standard deviation (SD) of the USEQ score in MS patients was not available, an estimation based on the maximum variance from the range SD=range/2 was considered. In the particular case of the total score of the USEQ, an estimated SD of 12 (in the most unfavorable case) was used. Considering a SD of 12 units, 32 patients in the VRR group will be sufficient to estimate a population mean of the total score of the USEQ with 95% confidence and a precision of ±4.3 units. A replacement rate of 5% has been anticipated.

Comparisons between the rehabilitation groups (VRR vs. CR) are planned for some secondary and exploratory outcomes. These objectives are assessed by scales or questionnaires that can be transformed to a 0–100 scale. In a scale of this range, a SD of 50 points for the mean of both groups can be assumed by the maximum variance principle. A difference of 20 points in the mean change between the two groups and a correlation coefficient of 0.90 will be assumed for each scale/questionnaire. Accepting an alpha risk of 0.05 and a beta risk of 0.2 in a two-sided test, 16 patients in the CR group and 32 patients in the VRR group are required to recognize a difference equal to or >20 units as statistically significant. A drop-out rate of 5% has been anticipated.

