### Statistical Analysis Plan

To address the primary objective, the total score for USEQ in the VRR group with measures of central tendency and dispersion (mean, SD, median, minimum and maximum) will be presented.

To compare mean changes after 6 months of VRR or CR on domains typically affected by MS (HRQoL, fatigue, ADL, work status, depression, anxiety, disability, spasms and spasticity, balance, and cognition) an inferential analysis will be used. For variables that follow a normal (or parametric) distribution, a *t*-test will be used. For variables that do not follow a normal (or parametric) distribution, Mann-Whitney (for unpaired data) or Wilcoxon (for paired data) hypothesis tests will be used. For the analysis of the contingency tables and comparison of proportions and/or frequency distributions, the chi-squared test (or Fisher's exact test where appropriate) will be used. All tests will be 2-tailed, and *p* < 0.05 will be considered significant.

To investigate therapy adherence and discomfort during the VRR program, a descriptive statistical analysis will be performed. Measures of central tendency and dispersion (mean, SD, median, minimum and maximum) will be presented.

The association between clinical and demographic characteristics and patient satisfaction with the VRR program will be calculated using Pearson or Spearman correlation coefficients, as appropriate.

Absent data will not be accounted for and will be considered missing data. No imputation will be done. Parameter estimates and 95% confidence intervals will be reported for the principal quantitative outcomes. The Statistical Package for the Social Sciences (SPSS) software (v 22 or later) will be used to conduct the analysis. Further details of data analysis will be provided in a statistical analysis plan.

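### Relapse, steroid use and certain medication changes end study participation after randomisation, so the 6-month VRR–CR comparisons cover only retained patients

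*Protocol article*

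**What the plan says.** Under Study Design, patients who have consented and met the selection criteria are allocated: "they will be randomized 2:1 to the VRR group or the CR group". The text under Figure 1 gives the reason. Neither randomisation nor blinding is needed for the primary aim, but "we decided to randomize the patients to prevent selection bias and allow comparisons between groups", meaning the secondary aims. The same paragraph blinds the assessors and states that the treating neurologist, physiatrist, physiotherapist and nurse know the arm.

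The Eligibility Criteria then carry three notes that act during the study:

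- Relapse, or methylprednisolone or equivalent: "Patients who have a relapse or who are treated with this medication during the study, as described above, will be discontinued from the study".
- Starting a drug that could change walking ability: also discontinued from the study.
- Changing a drug that, in the investigator's judgement, may interfere with rehabilitation results: "Patients in whom this medication is modified during the study will be excluded from the study".

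Each note ends participation in the study. None separates stopping rehabilitation from stopping assessment.

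The Statistical Analysis Plan section compares mean 6-month changes between arms by t-test or Mann-Whitney test, leaves absent data missing and states "No imputation will be done". For these comparisons, Sample Size Calculations states "A drop-out rate of 5% has been anticipated".

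**The concern.** A patient removed before month 6 has no V3 assessment, hence no 6-month change, and nothing stands in for it. The comparison becomes one of patients who had no relapse, no steroids and no relevant drug change.

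These events are not neutral. They bear on disability, walking, spasticity and fatigue, which are among the outcomes compared. They occur after allocation, and drug changes are made by clinicians who may know the arm. Removal may therefore depend on arm and on outcome together. Blinded assessors give no protection, because they do not see the removed patient at month 6.

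At stake is the property for which the protocol says it randomised. The removals also draw on a small allowance for loss, which lowers power.

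**Working it through.** **1. The plan's own figures.** Inputs from Sample Size Calculations: SD 50 on a 0–100 scale, correlation 0.90, difference in mean change 20, two-sided alpha 0.05, power 0.80, and 16 CR with 32 VRR.

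- SD of change = 50 × √(2 × (1 − 0.90)) = 22.36.
- Normal-approximation n for CR at 2:1 = (1.96 + 0.84)² × 22.36² × 1.5 / 20² ≈ 14.7, so 15 CR and 30 VRR.
- With 5% loss: 15/0.95 = 15.8, so 16; 30/0.95 = 31.6, so 32.

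The stated 16 and 32 reproduce, and they already contain the 5% allowance.

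**2. What the allowance covers.** 5% of 48 is 2.4 patients. That must absorb relapse, steroids, both medication rules and ordinary drop-out over 6 months.

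**3. Power under further loss.** Non-central t, two-sided 0.05, SE = 22.36 × √(1/n_CR + 1/n_VRR), non-centrality 20/SE. The protocol gives no removal rates, so the losses beyond the allowance are assumptions, taken as equal in both arms.

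| CR / VRR analysed | Lost of 48 | Power for 20 points |
|---|---|---|
| 16 / 32 | 0 | 81.6% |
| 15 / 30 | 3 (the size before the 5% inflation) | 79.0% |
| 14 / 28 | 6 (12.5%) | 76.0% |
| 13 / 26 | 9 (19%) | 72.7% |
| 12 / 24 | 12 (25%) | 69.1% |

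The fair reference is 15/30, where the plan expects to end. From there, 12.5% loss costs 3 points of power and 25% costs about 10. The normal approximation runs slightly higher (83.2% at 16/32, 80.7% at 15/30), with the same pattern.

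**4. Bias.** Let f be the share removed in an arm, and D the number of points by which removed patients would have done worse than retained ones. The all-randomised mean in an arm is the retained mean minus f × D, so

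retained difference − all-randomised difference = (f_VRR − f_CR) × D.

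| f_VRR | f_CR | D | Shift in VRR − CR |
|---|---|---|---|
| 10% | 10% | 20 or 40 | 0 |
| 15% | 5% | 20 | +2 |
| 15% | 5% | 40 | +4 |
| 5% | 15% | 20 | −2 |
| 5% | 15% | 40 | −4 |

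All of these inputs are assumed. D may even be negative, for instance if a newly started drug improves walking, and the sign then reverses. For scale, the SE of the difference at 16/32 is 22.36 × √(1/16 + 1/32) = 6.8 points, so 2 points is about 0.3 SE and a tenth of the 20-point target.

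**5. Primary outcome.** (1.96 × 12/4.3)² = 29.9, so 30, and 30/0.95 gives 32: the stated precision reproduces. With 10% removed (28.8 patients) the half-width is 1.96 × 12/√28.8 = 4.38; with 20% removed (25.6) it is 4.65. No between-arm comparison is involved.

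**The case against.** The strongest reply is that the damage is limited. The primary outcome is a single-arm description of USEQ, the protocol says randomisation is not needed for it, and the study calls itself a pilot for generating hypotheses. The rules also have a clear purpose: to keep relapse and drug effects from being credited to rehabilitation. The illustrated bias is small against the standard error and vanishes when removal and D are equal in both arms. All of this stands, and it lowers the severity.

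It could also be said that the analysis set belongs to the separate SAP. That is true of naming the set, but a SAP cannot supply month-6 assessments that the protocol has stopped collecting. Table 1 does label V3 as also a study completion visit. Even if that allowed an early exit assessment, which the text does not say, it would not be the 6-month change.

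Several stronger readings are tempting and are not supported:

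- *Patients who can no longer complete a walking test are dropped.* For the T25-FW the protocol states only that "the time limit per trial is 3 min"; it does not say how a timed-out trial is recorded. The 6 MWT is scored by distance, and nothing says a low or zero distance is treated as absent. Such scoring is commonly left to the SAP.
- *Data already collected are deleted.* Nothing says so. A patient discontinued after V2 could still contribute a month-1 change.
- *Any medication change removes a patient.* Beyond steroids, the rules cover only drugs that may interfere with rehabilitation results or could modify walking.
- *The bias favours a particular arm.* No event rates by arm are given.

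**Conclusion.** The point holds for the secondary 6-month VRR–CR comparisons: as written, they are comparisons of retained patients, which works against the stated reason for randomising. This follows from rules set out in the protocol, not from missing detail. The sample size itself is not wrong.

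The power figures rest on the plan's SD, correlation and 20-point difference, and on assumed loss rates beyond 5%. The bias figures of 2 to 4 points only illustrate the mechanism; actual size and direction cannot be derived from the document. For the primary USEQ mean, the effect is a narrower population (patients who stayed stable) and slightly less precision. This should be fixed, but it does not undermine the primary aim.

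**What to change.** Without changing any clinical rule on treatment or rehabilitation, reword the three notes in the Eligibility Criteria so that these events do not end study follow-up and V2 and V3 assessments are still collected. Record the event and its date. Make the main VRR–CR comparison one of all randomised patients in their assigned arm, and report the analysis excluding these events as a sensitivity analysis. Report the number of such events by arm. A larger sample would restore power but would not remove the bias.

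The cost is an amendment to the protocol wording and matching text in the SAP. V2 and V3 already exist and are held at routine clinical visits. There are two drawbacks. Relapse and drug effects add some noise to the main comparison, which the sensitivity analysis addresses. And half the participants were enrolled at submission, so the assessments of any already discontinued may not be recoverable; their number by arm should be stated.

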### Intervention

Patients will attend 8 on-site rehabilitation sessions during 4 weeks (2 sessions per week) of ~2 h duration each. The rehabilitation sessions will be conducted by a physiotherapist in groups of a maximum of 4 at the physiotherapy room of the Hospital Universitario de la Princesa in Madrid (Spain). Groups will be formed according to patients' functional level measured by the EDSS (36), resulting in three subgroups (low, medium, or high functional level) in each rehabilitation group (VRR and CR). The number of sessions conducted on site will provide sufficient training to allow patients to continue performing the rehabilitation exercises at home independently.

### Conventional Rehabilitation

#### Physical Exercises

All patients will receive CR on site (eight sessions in the CR group and four sessions in the VRR group). The rationale for including four sessions of CR in the VRR group is to ensure that all patients become familiar with all the exercises and learn to perform the movements correctly before doing them within the virtual environment. Patient status and suitability to perform the exercises (heart rate, blood pressure, temperature, and fatigue) as well as the temperature and humidity of the room will be evaluated at the beginning of each session.

During the rehabilitation sessions, exercises will be based on a standardized rehabilitation program (37) which has been extensively described elsewhere. Briefly, to ensure appropriate muscle activation, a 30-min warm-up with light aerobic activity and mobilization using the cycle ergometer or pedal exerciser will be performed. This will be followed by stretching, and exercises aimed at improving spasticity (~10–15 min), coordination and balance (~10 min), mobilization (~10–15 min), breath control (~10–15 min), and gait (~10–15 min). The exercises will be conducted in supine, prone, quadruped, knees and standing positions, and they will be interspersed with rest periods. Energy-saving techniques will be also taught during the sessions.

All exercises will be individually tailored according to the patient's abilities and needs. Exercises are classified according to the level of difficulty (low, medium, high), and patients will be assigned to a group (low, medium, and high function) based on an initial evaluation. Given that all patients in the group will have a similar level of function, patients will easily adapt to the pace of the session. During all sessions, patients will be led and supervised by the physiotherapist, who will give personalized instructions on the exercises according to the patient's function and ensure all the exercises are performed safely. For the last session, patients will be engaged to attend accompanied by a family member in order to serve as a reinforcement for rehabilitation at home. Patients will be requested to perform the exercises at home in the presence of a family member and after having removed all possible obstacles in the play area to increase patient safety.

#### Cognitive Exercises

The VRR program includes in its design a component of cognitive rehabilitation. Tasks performed in the virtual environment are designed to train alternating and sustained attention based on the Sohlberg and Mateer model (38). Patients in the CR group will perform a cognitive task that will allow them to stay cognitively active. They will be provided with a notebook containing several texts selected by a neuropsychologist and tailored to patient deficits. Patients will be required to read and summarize the text in ~ two lines, and they will be instructed to do one text each day they perform the physical exercises at home. This task is not based on any neuropsychological model of attention training.

#### Virtual Reality Rehabilitation

The software and hardware that will be used in the VRR group are discussed below. Briefly, a program with task-specific interactive games was specifically designed for MS patients by the multidisciplinary team involved in rehabilitation. Its design was based on the type of exercises performed during CR that is routinely conducted at the hospital and that has previously shown to be effective in improving motor symptoms in MS patients. The software allows the physiotherapist to select the exercises and level of difficulty of the exercises to be performed by the patient, and to follow the patient's progress. The hardware is composed of devices for visualization and recognition of body movements that are considered easy to use in the rehabilitation context.

